**Figure 1 figure1:**
[figure not shown]
Patient recruitment and flow. Numbers reflect planned enrollment based on power analyses and potential attrition. AA: African-American or Afro-Caribbean; Hisp: Hispanic; WNH: white non-Hispanic.

### Treatment Assignment

#### Inclusion and Exclusion Criteria

Participants will be eligible for the study if they are 40 years of age or older, are treated for at least one of the conditions in the Functional Comorbidity Index [90] (cardiovascular disease, arthritis, cancer, lung disease, osteoporosis, depression, and others) with at least one medication, have health literacy below the 8^th^ grade level as indicated by the REALM (English) or SAHLSA (Spanish), and are willing to participate for the length of the study. Potential participants will be excluded if they are not able to provide informed consent, have a cognitive or psychiatric disorder that impairs their ability to safely participate in the study, or are not able to remain involved over the full length of the study.

A screening procedure for the new project was developed by assessing the ability of the REALM [85] or SAHLSA [91] to predict if participants had an 8^th^ grade or lower level of reading on the Woodcock-Johnson or Muñoz reading tests. Using the R statistical package pROC [92], a score of 62 on the REALM predicted reading skills less than an 8^th^ grade level on the Woodcock-Johnson (area under the curve [AUC]=0.79, 95% CI 0.72-0.87; sensitivity=0.80, specificity=0.67) with similar results for the SAHLSA. Earlier analyses showed that the FLIGHT/VIDAS General Health Literacy (HL) scale will also be effective for use in detecting participants with lower levels of reading skills (all *P-* values <.001). Analyses did not differ for language groups (AUC for Spanish sample=0.86, *P*<.001).

#### Recruitment and Retention

Recruitment at the Atlanta sites will take place in the Primary Care clinics of Grady Health Services and Emory Healthcare. Grady Health Services is the largest public health provider in Georgia, and fifth largest in the nation, with more than 130,000 outpatient visits per year. Emory Healthcare has satellite clinics throughout metro-Atlanta and serves a broad array of patient demographics and backgrounds. In current studies, it is possible to access the electronic medical record to prescreen study participants. We will continue this practice after obtaining Institutional Review Board (IRB) permission. The study recruiter will identify potential participants meeting inclusion criteria; he or she will then meet with clinic staff and providers, supply them with study information (flyers, brochures), and ask the clinic staff/provider to give the study information to these potential participants. Passive recruitment through study flyers and information about the study on clinic phone-wait systems will also be used. All studies utilizing these procedures are currently on target with recruitment goals.

In addition to a pool of subjects who participated in prior studies and have given permission to contact them in future studies, Spanish-speaking Hispanics will be recruited from Nova Southeastern University internal, family, and geriatric medicine clinics. Special efforts will be made to recruit a diverse group of Hispanics representative of South Florida and the rest of country’s Hispanic population, per US census data, particularly with respect to country of reference and educational attainment. In our previous study, we recruited more than 320 Spanish-speaking Hispanics over 3 years of active recruitment [25-28].

#### Interventions

Participants in the experimental groups will use modules that are tailored on three key dimensions: (1) preferred language (English or Spanish), (2) level of health literacy (3^rd^ or 6^th^ grade), and (3) racial or ethnic relevance (using verbal and graphic elements that will enhance the relevance of the material to African-Americans, Hispanics, or non-Hispanic whites). In the experimental groups, the intervention will add a fourth dimension of tailoring by providing individual feedback on understanding, via ongoing assessment of learning and review of material that is not yet mastered. The intervention content will be closely linked to the ASK model of health literacy [26] by targeting skills and knowledge related to CDSM, as informed by results of the qualitative study in Phase 1.

Participants in the control group will view informational screens and answer questions similar to the experimental group, but materials will be presented at the standard and widely recommended 8^th^ grade reading level (the approximate average reading level of adults in the United States [93]) to simulate the literacy demands that participants typically encounter when using health care information. Materials will not be tailored for race or ethnicity, except that Spanish speakers will complete the intervention in their preferred language.

#### What Will Participants Actually Do?

A typical intervention session will begin with the participant being greeted by study staff and directed to a touchscreen computer station. The study assistant will ensure that the patient has begun the correct study module (eg, self-management of sleep problems). The participant will view screens that present basic information on types of sleep disorders and their causes. After presentation of a discrete amount of information, a review screen is presented to consolidate learning (eg, “Common causes of insomnia are…”). The next several screens will present questions to check participants’ learning; if questions are answered incorrectly, the program loops to a review of the topic with a second presentation and check question. Specific sections of the intervention will focus on improving information search skills via computer-coached materials that facilitate comprehension of written materials on insomnia (eg, “What is the major point of this paragraph?”) and Internet information search skills (ie, how to find more information on the Internet). In addition, coaching on interacting with health care providers (eg, writing down questions before visits, or taking a friend with you who can help you remember what the doctor says) will be woven throughout the modules.

### Procedures

Participants will be recruited through advertisements, publicity at local clinics and senior centers, and presentations at local organizations. After initial contact, participants will be scheduled for a screening visit during which their eligibility for the study will be established via an interview to assess demographics, current treatment for at least one health condition, and level of health-related reading using the REALM or SAHLSA. During the baseline visit, participants will complete cognitive and psychosocial assessments and be oriented to the health literacy intervention. This visit will include baseline assessment of participants’ health literacy with Form A of the General HL and Numeracy (NUM) scales of FLIGHT/VIDAS. Participants will then be randomly assigned to the control or active condition, with assignment to low or high health literacy within the active intervention group based on HL scores. Participants in all groups will then complete three weekly visits (approximately 2 hours long) during which they will complete the health literacy intervention. All participants will thus complete 6 hours of the intervention. Final level of material attained will be recorded for use as a covariate in analyses, since some participants may progress more rapidly than others. At the end of the five weeks, participants will complete a postassessment visit during which they will complete Form B of the HL and NUM scales, along with the other outcome measures. Three months after this follow-up visit, participants will be asked to return for a final follow-up visit during which they will complete Form C (a combination of items from Forms A and B) of the HL and NUM scales and the same postintervention assessments of general health, activation, self-efficacy, and self-reported treatment adherence. At each follow-up visit, only measures hypothesized to be affected by the intervention will be administered. See Multimedia Appendix 1 for a detailed schedule of assessments.

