### Data Analyses

#### Initial Data Management

Initial review will evaluate data for completeness and valid characteristics through inspection of descriptive statistics. Although every effort will be made to minimize loss to follow-up, we recognize that some attrition is likely to occur. We will evaluate patterns of missingness in the data and follow widely-recommended procedures for dealing with this issue [109]. If our evaluation shows that missing data can be considered as missing at random (MAR) then our use of full-information maximum likelihood routines in MPlus statistical software (Muthén & Muthén; Los Angeles, California) will result in unbiased estimates of parameters [110]. If data are not MAR, we will include pattern of missingness in random effects pattern mixture analyses [111]. Group equivalence on demographic characteristics (except those defining group membership) and baseline measures not used in assignment will be assessed, and if differences are found these variables will be used as covariates in analyses. Other analyses will evaluate the distributional properties of dependent variables to assess the suitability of planned statistical models.

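### Final level of material attained, known only after randomisation, is planned as a covariate without restriction; in the efficacy models the arm contrast would no longer estimate the effect of assignment

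*Protocol article*

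**What the plan says.** The Procedures section gives the order of events. Baseline assessment includes Form A of the health literacy (HL) and numeracy scales. Then: "Participants will then be randomly assigned to the control or active condition, with assignment to low or high health literacy within the active intervention group". Three weekly sessions of about two hours follow, then the post-assessment with Form B and a later follow-up with Form C. On the variable at issue the section says: "Final level of material attained will be recorded for use as a covariate in analyses". The reason it gives is that participants may differ in how fast they advance.

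The Phase 2 Interventions section ties the material to arm. Experimental participants receive material at 3rd or 6th grade level, with a further element described for the experimental groups: "providing individual feedback on understanding, via ongoing assessment of learning and review of material that is not yet mastered". For the control group, "materials will be presented at the standard and widely recommended 8^th^ grade reading level".

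Under Data Analyses, Aim 1 names race/ethnicity, age, education and cognition as examples of covariates in a repeated-measures mixed model covering all three assessments. Aim 2 tests Hypotheses 3 and 4 in mixed models with covariates described only as relevant, one model per outcome, and compares estimated marginal means. Level attained is not named there. Nor is its use limited anywhere else, and the article does not say whether level means reading grade or progress through the modules.

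**The concern.** Hypothesis 3 is a randomised comparison, so its estimate should be the effect of being assigned to the tailored intervention. Level attained is partly a result of that assignment. The reason given for using it, that some people progress faster, describes a response to the assigned material.

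Conditioning on it does two things. It removes whatever part of the effect works through progress. It also compares participants who reached the same level under different material, and these will tend to differ in ability and motivation. Randomisation no longer protects that comparison. At stake is whether the main efficacy contrast can be read as a treatment effect.

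**Working it through.** The article gives no numerical effect size, correlation or definition of level, so there is no figure of the plan's own to reproduce. The check is a reading of the timing followed by an illustration. All parameter values below are assumptions, in SD units.

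**1. Timing and dependence on arm.** Procedures places randomisation before the sessions and level attained after them. Interventions gives the arms different grade levels and describes feedback with review as an addition for the experimental groups. Either feature could change how far or how fast a participant goes.

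**2. Inputs (assumed).** Arm raises progress by a = 0.5. Ability raises progress by p = 0.6 and the outcome by q = 0.5. Progress raises the outcome by m = 0.3. The direct effect of arm is d = 0.1. Ability has variance 1 and progress has within-arm variance 1, so its residual variance is 1 - 0.6² = 0.64.

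**3. Total effect against adjusted effect, ability unmeasured.**
- Total: d + a·m = 0.1 + 0.5 × 0.3 = 0.25.
- At equal progress, active participants have ability lower by p·a = 0.6 × 0.5 = 0.30, which lowers their outcome by 0.5 × 0.30 = 0.15.
- Adjusted: d - a·p·q = 0.1 - 0.15 = -0.05.

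A simulation with 1,000,000 participants gave 0.250 and -0.052.

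**4. Allowing for measured ability.** If baseline covariates capture a share f of the variance of ability, the adjusted arm effect is

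d - a·q·p(1 - f) / [p²(1 - f) + 0.64]

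| f | Calculation | Adjusted effect |
|---|---|---|
| 0 | 0.1 - 0.25 × 0.60/1.00 | -0.05 |
| 0.25 | 0.1 - 0.25 × 0.45/0.91 | -0.02 |
| 0.44 | 0.1 - 0.25 × 0.336/0.842 | 0.00 |
| 0.50 | 0.1 - 0.25 × 0.30/0.82 | 0.01 |
| 0.75 | 0.1 - 0.25 × 0.15/0.73 | 0.05 |
| 1 | 0.1 - 0 | 0.10 |

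The sign changes only when f is below about 0.44. Even with ability fully measured the result is 0.10, the direct effect, and not 0.25, the effect of assignment.

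**5. Direction.** With ability unmeasured, adjusted minus total is -a(m + p·q) = -0.6a. If arm does not affect progress (a = 0), both are 0.10 and there is no bias. If arm slows progress (a = -0.5), the total is 0.1 - 0.15 = -0.05 and the adjusted value is 0.1 + 0.15 = 0.25. The bias can therefore go either way.

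**6. Which quantity is affected.** A separate large-sample calculation (60,000 participants, three visits, complete data) assumed that arm shifts level by 1, level adds 0.3 per unit, and the direct effect is 0.1, so the true total is 0.40. Ability affects both level and outcome and is unmeasured.

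| Quantity | Without level | Level as constant main effect | Level × time |
|---|---|---|---|
| Time-by-arm interaction | 0.39 | 0.39 | 0.09 |
| Post-treatment difference in marginal means | 0.40 | -0.36 | not computed |

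A term constant over time cancels from change since baseline, so the interaction is untouched. The marginal-mean difference is not protected, and the level × time model returns roughly the direct effect alone. An ANCOVA of the first follow-up on baseline moved from 0.39 to -0.13 when level was added.

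**The case against.** The strongest reply is that the analysis section does not list level attained. Aim 1 names four baseline-type covariates, Aim 2 says only that relevant ones will be used, and Procedures does not say which analyses will take the variable. The fuller plan, not shown, may restrict it. This stands to the extent that one cannot say the efficacy models will contain it. It does not remove the point: the article states an intended use and sets no limit.

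The dependence on arm is also inferred. The section on what participants will do describes a review loop for a typical session without naming an arm, and controls answer similar questions. If arm did not affect level attained there would be no bias. Given the different grade levels, that is hard to assume in advance.

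Three stronger readings are tempting and are not supported.

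- *That the sign of the result would reverse.* This holds in the illustration only if measured covariates capture less than about 44% of ability. The plan measures cognition, education and academic skills, and names the first two as covariates.
- *That the arms cannot overlap on level (3 or 6 against 8), so the contrast is pure extrapolation with a spurious effect of 1.1 to 1.5 SD.* Level is undefined, and progress through modules fits the stated reason at least as well as reading grade. The Content section plans versions at 3rd, 6th and 8th grade for each intervention group. The figure also requires level to be fixed at assignment and baseline HL to be left out. With level fixed and Form A HL in the model, the same simulation gives -0.002 to -0.005.
- *That the baseline rule in Initial Data Management ("if differences are found these variables will be used as covariates in analyses") is a defect of the same kind.* It concerns baseline variables, and Aim 1 names prognostic covariates regardless of balance. Choosing covariates from observed imbalance is a lesser matter and does not bear on this point.

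**Conclusion.** The concern holds in this form: the article plans a post-randomisation covariate that plausibly depends on arm, without restricting its use. In the Aim 2 models, the adjusted marginal means or any level-by-time model would not estimate the effect of assignment for Hypothesis 3.

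Size and direction are unknown, because the documents give no figures. In the main illustration a true 0.25 becomes anything from -0.05 to 0.10, depending on how well ability is measured. Other assumed values move the estimate upwards, or not at all. The conclusion rests on arm affecting level attained, together with either an effect of level on the outcome or a shared cause that the covariates do not capture. A time-by-arm interaction with level entered only as a constant main effect, and complete data, is exempt.

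**What to change.** Replace the sentence in Procedures, and align the Aim 2 analysis text, so that:

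- final level attained is excluded from every model that estimates the arm effect;
- it is defined (reading grade or progress through modules) and reported descriptively by arm, or used in a labelled exploratory exposure or mediation analysis;
- efficacy models adjust only for baseline covariates, keeping those Aim 1 names (race/ethnicity, age, education, cognition);
- the baseline value of each outcome is handled through the planned repeated-measures model, where it is already one of the responses, and is not added again as a covariate.

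The cost is a change of wording in the protocol and analysis plan. No new data are needed, the variable can still be recorded, and the sample size does not change.

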#### Randomization and Blinding

After confirmation of eligibility, participants will be randomized to treatment condition according to a computer-generated schedule using the randomization procedures available in Research Electronic Data Capture (REDCap) electronic data capture tools hosted at Nova Southeastern University [94]. The principal investigator at each site ([name], [name]) will be responsible for each treatment assignment.

#### Measures

Primary outcome measures will be health literacy (FLIGHT/VIDAS), self-reported general health (Medical Outcomes Study 36-item Short Form; SF-36 [95]), health self-efficacy (Chronic Disease Self-Efficacy Scale [96]), patient activation (Patient Activation Measure [97]), and treatment adherence. Additional data will provide the ability to consider race, ethnicity, age, and other variables as potential confounders. These data will include demographic variables, mood [98], stress [99], patient-provider relationships [100], treatment engagement, general cognitive abilities, academic skills, health conditions, current symptoms, health care attitudes, self-efficacy [101], and health care utilization.

Severity and number of health conditions will be assessed with the Functional Comorbidity Index [90], a previously validated measure linked to physical status, and an index based on the Midlife in the United States study [102] protocol, as used in our earlier study [27], to allow comparisons with data from that study. Assessments will include information on the specific symptoms of key problems in chronic disease management, and will allow a pre/postevaluation of the effects of the intervention on each. Simple measures of physical status (walking speed [103], body mass index [104], and waist-hip ratio [105]) will also be obtained to assess the effects of health literacy, cognition, and comorbidity on these variables, as they have all been related to risks for mortality [6,106,107].

Most self-report instruments will be administered via Automated Computer-Assisted Self-Interview (ACASI) software with assessment materials presented on touchscreen computers. This strategy enhances data collection by allowing participants anonymity in their responses and reduces issues with hand scoring of measures and manual data entry. Both sites will use the ACASI software Questionnaire Development System (QDS; Nova Research, Bethesda, Maryland). Individually administered measures, including assessments of cognitive, academic, and health literacy status, will be hand scored and verified. QDS output files will be transferred between sites using encrypted file transfer technology also available in REDCap.

The intervention will be standardized by its computer-based presentation across sites, but assessments and interactions with site workers must also be standardized to ensure fidelity across sites. Procedures will be standardized via visit flow sheets accompanied by training and monitoring visits by the investigators at each site. To ensure secure retention delivery of data across sites, all data will be entered into the REDCap software twice [94]. Each entry will be compared using utilities in REDCap and discrepancies will be resolved via inspection of original paper-based data collection instruments.

#### Data Safety and Monitoring

All assessment procedures planned in this study are either standard psychological or educational procedures (or are similar to standards), and all interventions are similar to typical educational interventions, so we believe that all interventions are associated with minimal risk to participants. We do not anticipate the need for a formal data safety monitoring board for this study, but we will follow a data safety monitoring plan. The plan will require ongoing monitoring of participants’ reactions to assessment and intervention activities with formal logs recording any events suggestive of participant distress, frustration, or boredom. All study personnel will be instructed on the importance of recording any relevant events in study logs, the contents of which will be reported on a monthly basis to the principal investigator for minor incidents, and immediately for any serious event (eg, substantial indication of participant distress such as crying, expression of desire to discontinue participation due to emotional upset, or request for emotional assistance due to of feelings or thoughts triggered by assessments). All events will be tracked and reviewed via regular conference calls with site principal investigators for determination of what changes in study procedures should be made to ensure the safety of participants.

Given the length of the study and frequency of study visits, we will be able to maintain close contact with all participants in an ongoing fashion. We will be able to develop and maintain a relationship with each participant that facilitates communication about their reactions to the study. Study personnel will be trained to be alert for signs of emotional upset or frustration in participants as a reaction to study procedures, and will be proactive in approaching participants about their emotional states. Participants will be offered supportive counseling if indicated, and referral for other services if needed.

Finally, we will routinely assess (both formally and informally) participants' reactions to the study using interviews and an ACASI questionnaire that will allow them to privately express any concerns or problems related to the study. We will actively monitor participants' experience in the study, both informally in exit interviews and formally via their responses to ACASI questionnaires, to determine if the study is excessively stressful or upsetting.

